#### Secondary outcomes

##### School practices

Secondary outcomes will include the mean number of PA practices achieved and the proportion of schools meeting each of the practices (Table 1). Analysis will be undertaken similarly to the primary outcome, with a normal distribution function for the mean number of practices outcome.

##### Student level measures (nested sub study)

Student data will be analysed if accelerometers are worn for ≥480 min per day on ≥3 days [65]. Appropriate cut-points based on emerging evidence and expert advice for wrist worn accelerometers will be used to categorize different intensities of PA [66]. Analysis will use all available data and follow the intention to treat principle. Analysis of minutes of MVPA per day (overall, within school hours as determined by school timetables) at each of the two follow-up time-points (corresponding to 12 and 24 month follow-up) will be undertaken using linear mixed models, including school level random intercept to model the clustering (30 clusters) of students within schools, and a random intercept for individuals. Analyses will adjust for demographic characteristics (sex, age, Aboriginal and Torres Strait Islander background). Least square mean differences between intervention and control students will be presented at both time points, together with 95% confidence intervals and *p*-values. A similar analysis will be undertaken for anthropometry outcomes, weight, BMI, BMI z scores. Exploratory subgroup analyses will be undertaken by sex, Aboriginality and LOTE.

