**Fig. 1 Fig1:**
[figure not shown]
Consort Flow Diagram

The research will be conducted and reported in accordance with the requirements of the Consolidated Standards of Reporting Trials (CONSORT) Statement [31, 32] and the Standards for Reporting Implementation Studies (StaRI) Statement [33]. Secondary schools will be randomised to receive either the multi-component implementation support intervention, or to a control arm (usual school practices) after baseline data collection. Assessment of school PA practices will occur at baseline, 12 months (mid intervention) and 24 months. A nested study involving 15 schools per arm will be used to evaluate student level outcomes, objectively measured student PA via accelerometers (overall minutes of MVPA per day, and minutes of MVPA within school hours) and indicators of adiposity (weight, Body Mass Index (BMI)), measured at 12 and 24 months (Fig. 1). Approval will be obtained from relevant ethics committees. The trial has been prospectively registered ACTRN12617000681358.

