#### Student level variables (nested sub study)

*Physical activity:* Whole-day objective PA measurement will be undertaken using wrist worn Actigraph GT9X-BT or GT3X+ accelerometers [48], distributed to students at school within class, at the same time as students’ complete anthropometric measures and surveys. Accelerometers have displayed acceptable intra- and inter-instrumental reliability and provide a valid and reliable estimate of PA in young people [48, 49]. Students will be asked by trained research assistants to wear the accelerometers on their non-dominant wrist during waking hours for seven consecutive days. To improve compliance, student and/ or parent mobile phone numbers will be requested via the consent form, and a text message sent by the researchers each morning reminding students to wear the accelerometer [15]. School start and finish times that apply during the assessment period will be requested from schools.

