### Sample size

Based on publicly available data there are approximately 120 potentially eligible schools. Based on school consent rates in previous trials conducted by the researchers of around 65–70% [15], a sample of 76 schools (38 per arm) will provide 80% power to detect an absolute increase of ~ 35% between groups in the proportion of schools implementing at least 4 of the 7 items at 12 and 24-months (alpha 0.025 to allow for program effect at 12 or 24 months). Without prior data on baseline levels of school practices, this calculation makes the conservative assumption that 40% of schools in the usual care arm achieve this target at follow-up.

For student level variables it is estimated that a nested sample of 30 schools and a student consent rate of 65% will yield about 1200 students (600 per group) with valid accelerometer data. Using an ICC of 0.03 [15] and a standard deviation of 23 min of MVPA, will allow a 6.2 min [47] difference in the mean difference between groups at each separate follow-up to be detected with 80% power and a 2.5% type 1 error rate.

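### One whole-day wear rule also decides who enters the school-hours MVPA analysis, and it does not check that school hours were observed

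*Protocol article*

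**What the plan says.** The wear rule is in the Protocol article, Statistical analyses, under Student level measures (nested sub study): "Student data will be analysed if accelerometers are worn for ≥480 min per day on ≥3 days". It names no type of day and no time window. The same paragraph adds "Analysis will use all available data and follow the intention to treat principle" and then names two outcomes: "Analysis of minutes of MVPA per day (overall, within school hours as determined by school timetables". No second wear criterion is given anywhere in the article.

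School-hours MVPA is a named student outcome. The Study design section lists "overall minutes of MVPA per day, and minutes of MVPA within school hours" together.

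The data collection section, Student level variables (nested sub study), asks students to "wear the accelerometers on their non-dominant wrist during waking hours for seven consecutive days". It also states: "School start and finish times that apply during the assessment period will be requested from schools". The timetable is therefore available, but the article uses it only to mark out the school-hours window, not to judge whether the device was worn inside it.

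**The concern.** A wear rule should establish that the period being analysed was observed. A requirement of 480 minutes at any time of day does this reasonably for whole-day MVPA. For school-hours MVPA it can fail in two directions: it can reject a student whose school hours were fully recorded, and it can accept one whose school hours were barely recorded.

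This matters because school-hours MVPA is the student outcome closest to what the program changes. In Table 1, the practices on PE lessons, school sport, and recess and lunchtime activity all act during school, and the policy practice sets a target for activity in school time. Losing informative students, or keeping students with a single school day, weakens the comparison best placed to show a student-level effect.

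**Working it through.** **The plan's own figure.** The only stated figure that depends on valid accelerometer data is the detectable difference of 6.2 minutes in the Sample size section. Its inputs are 1200 students (600 per group), 30 schools, ICC 0.03, SD 23 minutes, 80% power and 2.5% type 1 error, taken here as two-sided.

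- Students per school: 1200 / 30 = 40.
- Design effect: 1 + (40 − 1) × 0.03 = 2.17.
- Effective sample per group: 600 / 2.17 = 276.5.
- Standard error: 23 × √(2 × 2.17 / 600) = 1.956 minutes.
- Normal approximation: (2.241 + 0.842) × 1.956 = 6.03 minutes detectable, and 82.3% power at 6.2.
- t distribution with 28 degrees of freedom: 6.30 minutes detectable, and 78.4% power at 6.2.

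The two variants bracket 6.2, so the figure reproduces. It already counts only students with valid data ("will yield about 1200 students (600 per group) with valid accelerometer data") and does not say which MVPA outcome it covers. The present point does not alter it.

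**Inputs for the wear check.** From the article: 480 minutes, 3 days, and seven consecutive days of wear, which contain five weekdays and two weekend days. The lengths of the school day and the waking day are not given. I assume 360 to 400 minutes for school and 840 to 960 minutes (14 to 16 hours) awake.

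**(a) Complete school-hours wear, little otherwise.** The daily shortfall is 480 minus the school day:

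- 480 − 400 = 80 minutes.
- 480 − 360 = 120 minutes.

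A student who wore the device for all of school on five weekdays and not outside school on those days has no valid weekday. Even two fully worn weekend days give 2 valid days, below the 3 required. The student is excluded with school hours fully recorded. The direction needs only a school day shorter than 480 minutes (8 hours).

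**(b) Number of school days.** Two of the three required days may be weekend days: 3 − 2 = 1. A student can therefore qualify with one school day. This follows from the article alone.

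**(c) School-hours wear on a valid school day.** Waking time outside school is the waking day minus the school day, and the school-hours wear needed to reach 480 is max(0, 480 − that time).

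| Waking day (min) | Outside school, for a school day of 400 to 360 min | School-hours wear needed |
|---|---|---|
| 840 | 440 to 480 | 40 to 0 min (10% to 0% of the school day) |
| 900 | 500 to 540 | 0 |
| 960 | 560 to 600 | 0 |

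With a waking day of 15 to 16 hours, a school day can count as valid with no wear during school. With 14 hours, at most 40 minutes of school-hours wear is needed.

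**The case against.** **The article is condensed.** Accelerometer processing rules are often left to the analysis plan, and one that is not at hand might add a school-hours criterion. The rule's wording is also general: read literally, it would make even weight and BMI depend on accelerometer wear, which can hardly be meant. This is fair, but the article does not leave wear validity open. It fixes a specific rule and places both MVPA outcomes under it in one paragraph. The statement about using all available data does not waive that rule.

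**The extreme patterns are unlikely.** With a 900-minute waking day, a valid day without school-hours wear needs 480 of the 500 to 540 out-of-school minutes (480/540 = 89% to 480/500 = 96%). A full school-day wearer needs only 80 of 500 (16%) to 120 of 540 (22%) to qualify, and is dropped only after falling short on at least five of seven days. Students are told to wear the device while awake, receive it in class and get a reminder each morning. This stands, and it limits the likely number affected.

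**Stronger readings are not supported.**

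- A reader might infer that unworn school time enters as inactivity and dilutes the group contrast. The article does not say how non-wear is scored; it may be treated as missing.
- A reader might infer bias between the arms. That needs wear habits to differ by arm, and nothing in the article shows that they do.
- A reader might infer that weekend days add zeros to school-hours MVPA. The outcome is taken "overall, within school hours as determined by school timetables", so weekend days contribute no school-hours minutes. What remains is the small number of school days.

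**One analysis set keeps the two outcomes comparable.** That is a legitimate aim, and a sensitivity analysis can serve it.

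**Conclusion.** The concern holds as a mismatch between a stated rule and one of its two outcomes. Applied as written, the rule excludes students with complete school-hours wear if the school day is shorter than 8 hours and they wore the device little otherwise. It also admits students on the strength of one school day. Only the statement that this one day could have little or no school-hours wear depends on the assumed waking time.

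The sure consequence is that the rule can discard usable school-hours data and lose precision. Understatement of school-hours MVPA is conditional on zero-scoring of unworn time. The number of students affected, and so the size of any effect on the estimate, cannot be derived from the article.

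The point concerns one secondary outcome in the nested study. The primary outcome, whole-day MVPA and the 6.2-minute calculation are untouched. It should be corrected before the student data are analysed.

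**What to change.** Keep the 480-minute, 3-day rule for whole-day MVPA. For school-hours MVPA, replace it with a pre-specified rule that uses school days only:

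- a school day is valid if the device was worn for a minimum share of that school's timetabled minutes (80% would be one example; the article gives no basis for a particular value);
- a student enters with a stated minimum number of valid school days;
- school days below the threshold are set to missing, and no 480-minute requirement applies.

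The cost is one further processing step on data already planned, since school start and finish times will be requested in any case. The two MVPA outcomes will have slightly different analysis sets. A sensitivity analysis of both in the students who meet both rules would show whether that matters.

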### Randomisation

Consenting schools will be randomised to either program or control condition using a random number function in Microsoft Excel. Block randomisation (1:1) will be undertaken within the strata (four local health districts and two school sectors). Principals will be notified of their school allocation following baseline collection of school practice measures. Schools consenting to student level data (nested study) will be randomly selected within strata using a random number generator in Excel, and at stratum sizes proportional to that observed in the main study. Schools will be notified of student level measurement involvement when notified of group allocation.

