#### Primary outcomes

The primary outcome is the proportion of schools implementing at least four of the seven PA practices [47] based on the Head PE teacher computer assisted telephone interview data. The analysis will follow intention-to-treat principles, with multiple imputation the primary method of dealing with missing data. Per protocol analyses will also be performed, based on those schools receiving the full implementation support intervention.

Differences between treatment groups in the primary outcome at 12 and 24-months will be assessed using generalised linear regression models (a separate analysis conducted for each time point). A log link and binomial distribution function will be used (a logistic link will be utilised if the analysis model fails convergence). The stratification variables will be included in the models as covariates.

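### The student-level models leave out district and sector, the strata used for randomisation and nested selection; if these predict the outcome, inference is conservative and some power is forgone

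*Protocol article*

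**What the plan says.** All references are to the protocol article.

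- **Randomisation, allocation of schools:** "Block randomisation (1:1) will be undertaken within the strata (four local health districts and two school sectors".
- **Randomisation, nested sample:** schools that consent to student measures "will be randomly selected within strata using a random number generator in Excel, and at stratum sizes proportional to that observed in the main study". Whether the two arms are balanced within each stratum of this subsample is not stated. Study design gives only the totals: "A nested study involving 15 schools per arm will be used to evaluate student level outcomes".
- **Primary outcomes:** "The stratification variables will be included in the models as covariates".
- **Secondary outcomes, School practices:** "Analysis will be undertaken similarly to the primary outcome, with a normal distribution function for the mean number of practices outcome". This carries the strata over to the school-level secondary outcomes.
- **Secondary outcomes, Student level measures:** a linear mixed model "including school level random intercept to model the clustering (30 clusters) of students within schools", plus a random intercept for individuals. On covariates: "Analyses will adjust for demographic characteristics (sex, age, Aboriginal and Torres Strait Islander background". Nothing here refers back to the primary model.
- **Same section, adiposity:** "A similar analysis will be undertaken for anthropometry outcomes, weight, BMI, BMI z scores". The covariate list therefore applies to weight and BMI as well.

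**The concern.** Stratified allocation removes differences between districts and sectors from the comparison of the arms. A model without the strata still counts those differences in the between-school variance. Where the strata predict the outcome and the arms are balanced within them, the reported standard error then exceeds the true one: intervals are too wide, the test rejects less often than its nominal level under the null, and precision that the design has already paid for is not used.

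If the 30 nested schools happen not to be balanced by arm within strata, the loss takes another form. A chance difference in district or sector mix between two groups of 15 schools stays in the estimate.

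The between-school component matters here because there are only 30 clusters. Students are measured only at 12 and 24 months, so no baseline value of the student outcome can absorb school differences. The student results also feed the cost-effectiveness ratios.

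This is more than detail left to a fuller document. The article states a specific covariate list for these models, and it differs from the treatment of the strata two subsections earlier.

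**Working it through.** **Inputs from Sample size and Study design.** 30 schools (15 per arm); about 1200 students with valid data, so 1200/30 = 40 per school; ICC 0.03; SD 23 min; difference 6.2 min; type I error 2.5% (taken as two-sided); stated power 80%.

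**Input not in the documents.** R2, the share of between-school MVPA variance explained by district and sector. Assumed range: 0 to 0.50.

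**Step 1: reproduce the stated power, without strata.**

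- Design effect = 1 + 39 × 0.03 = 2.17. Effective n per arm = 600/2.17 = 276.5.
- SE of the difference = 23 × √(2/276.5) = 1.956 min. The ratio 6.2/1.956 is 3.17.
- Normal approximation: power 82.3%, detectable difference 6.03 min.
- Noncentral t with 30 − 2 = 28 df: power 78.4%, detectable difference 6.32 min.

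The stated 6.2 min at 80% lies between the two, so the planned figure is reproduced without any stratum adjustment.

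**Step 2: add the strata (analytic).** In units of SD², the variance of a school mean is 0.03 × (1 − R2) + 0.97/40 = 0.03 × (1 − R2) + 0.02425. The SE is 23 × √(2 × variance/15). Three district terms and one sector term leave 28 − 4 = 24 df.

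| R2 (assumed) | Variance of school mean | SE, strata in model | Unadjusted SE 1.956 ÷ this | Power, 24 df |
|---|---|---|---|---|
| 0 | 0.05425 | 1.956 | 1.000 | 77.6% |
| 0.10 | 0.05125 | 1.901 | 1.029 | 80.1% |
| 0.25 | 0.04675 | 1.816 | 1.077 | 83.9% |
| 0.50 | 0.03925 | 1.664 | 1.176 | 90.1% |

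At R2 = 0 the cost of adjusting is 78.4 − 77.6 = 0.8 points. Adjustment breaks even at R2 of about 0.03. With all eight strata as separate cells (21 df), break-even is about 0.06 and power at R2 = 0 is 76.9%.

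**Step 3: what the unadjusted model reports (simulation).** 30 school means were simulated with arms balanced within assumed strata and analysed without and with the strata.

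| R2 (assumed) | Reported SE, no strata | True SE | Type I error, no strata (nominal 0.025) | Power without strata | Power with strata |
|---|---|---|---|---|---|
| 0 | 1.94 | 1.96 | 0.025 | 78.7% | 78.0% |
| 0.10 | 1.94 | 1.92 | 0.021 | 78.2% | 79.5% |
| 0.25 | 1.95 | 1.81 | 0.016 | 79.8% | 84.0% |
| 0.50 | 1.96 | 1.67 | 0.008 | 81.1% | 90.1% |

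At R2 = 0.25 the reported SE is about 8% too large (1.95/1.81), and at 0.50 about 17% (1.96/1.67). With the strata in the model, type I error stayed between 0.024 and 0.026. The simulated powers agree with the analytic ones to within about one point. At R2 of 0 and 0.10 the small differences between reported and true SE are of the order of simulation error.

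**Adiposity.** No SD or ICC is given for weight, BMI or BMI z score, so the same calculation cannot be made.

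**The case against.** The strongest reply is that the harm is conditional. Nothing in the article says how strongly district or sector predicts student activity. All nested schools are co-educational, not fully selective and in the more disadvantaged half of areas, so differences between strata may be modest. At R2 near zero, adjustment gains nothing and spends degrees of freedom. These are secondary outcomes, and any error is in the conservative direction. All of this stands, and it is why the size is given as a range starting at zero. The article does offer some reason to expect differences: the districts run from major city to regional and rural, and the weekly activity minimum is described as policy for government schools. Neither fact fixes R2.

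Four stronger readings are tempting but unsupported:

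- **That the standard errors are too large as a matter of fact.** This needs both a material R2 and balance by arm within the nested strata. The documents establish neither.
- **That the study is underpowered.** The stated 80% is reproduced without the strata. What is forgone is a possible gain over plan.
- **That the estimates are confounded by district or sector.** Allocation and nested selection are both random, so any imbalance is due to chance. Inflated standard errors presuppose balance and unadjusted imbalance presupposes its absence, so the two do not apply together within the same strata.
- **That other school-level covariates, such as a baseline practice score, are also needed.** That score is not a stratification variable, and nothing in the article shows that it predicts student outcomes.

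It can also be said that an article is condensed and its covariate list may not be exhaustive. The list is specific, however, and contrasts with the explicit inclusion of the strata in the primary model.

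**Conclusion.** The point holds in conditional form. As written, the student-level models omit the variables that structured both the randomisation and the nested selection, and they depart from the article's own school-level models.

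For MVPA, under the article's ICC, SD and numbers and with arms balanced within strata, the forgone power is nil or slightly negative at R2 = 0, about 1 to 2 points at 0.10, about 4 at 0.25 and about 9 at 0.50. Over the last two values, type I error falls to about 0.016 and 0.008 against 0.025. If the arms are not balanced within the nested strata, the gain from adjusting is removal of chance imbalance instead. R2 is an assumption throughout. No false-positive risk is shown.

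The change is still worth making, because its worst case is under one power point and its benefit may be several.

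**What to change.** In the student-level section, add local health district (three indicator terms) and school sector (one) as fixed effects to every MVPA and anthropometry model, alongside sex, age and Aboriginal and Torres Strait Islander background. This matches the primary model. Main effects are preferable to eight separate strata, which would leave 21 rather than 24 school-level degrees of freedom. It would also help to state whether the nested schools are balanced by arm within strata.

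The cost is one sentence of text and about four of 28 school-level degrees of freedom. No new data are needed, since district and sector are known for every school, and the sample size statement need not change.

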### Economic analyses

The economic evaluation will be performed as a within-trial analysis, indicating that only costs and effects that accumulate within the trial duration are included. In this study, the prospective, trial-based economic evaluation will involve (i) resource use modelling to describe the investment required to develop and execute the implementation-intervention from all relevant stakeholder perspectives; (ii) a cost consequence analysis to identify, measure and value all associated costs and outcomes associated with the program compared to usual practice and (iii) subject to assessment of effectiveness, a cost-effectiveness analysis based on both primary school level outcome and secondary, student level outcomes.

